#### Strategies to improve adherence to interventions {11c}

To minimize data loss, all the participants in the trial will receive a card with the date and time of session. The therapist responsible for the session will send a WhatsApp message from a cellphone account used only for this research, confirming the session, 1 day in advance. For the evaluations and reevaluations, the blinded evaluator will contact the participants by WhatsApp, confirming the initial and final evaluations, as well as the follow-up 1 month after the end of the intervention, which will be performed by telephone. In cases of abandonment or impossibility of continuing the study, the data will be analyzed according to an intention-to-treat protocol.

#### Relevant concomitant care permitted or prohibited during the trial {11d}

Concomitant treatments such as continuous use medications for hypertension and diabetes will be permitted during the trial. The participants will not be permitted to start any new type of intervention or activity during the trial period.

#### Provisions for post-trial care {30}

Individuals will be treated in one session, and they will receive a document with all the care that must be considered. In addition, they will have the telephone numbers of the researchers and the department where the study will be carried out. They will also receive a diary of records of medications consumed after the proposed therapies. The individuals will be monitored for 1 month after the intervention and will be reassessed by phone. The therapies normally do not bring greater health risks to those who participate. However, if in any case the individual has any adverse effect, he/she will be referred to the University’s health center for specific care.

### Outcomes {12}

The primary outcome will be the pain intensity. It will be evaluated using the numerical rating scale (NRS). Secondary outcomes will be as follows: pressure pain threshold (PPT), temporal summation of pain (TS), conditioned pain modulation (CPM), use of analgesic medications after treatments, and Global Perceived Effect Scale (GPE). These outcomes will be evaluated before and after the treatments. Evaluation using the NRS and the global perceived effect scale will be performed at the end of the 1-month follow-up period.

#### Numeric Rating Scale (NRS)

The NRS employs a simple and easy-to-use scale, where the individual is asked to indicate the intensity of the current pain, using a scale ranging from 0 (“no pain”) to 10 (“worst pain imaginable”) [54]. The participants will be instructed to rate the pain experienced at rest and during movements (flexion, extension, lateral inclination to the left and right, and rotation to the left and right). All before-after data will be individually recorded and compared for their respective positions.

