#### The primary objective

The primary objective is to assess the pain intensity at rest and during cervical active movements (flexion, extension, left and right lateral bending, and left and right rotation) using the Numerical Rating Scale (NRS), immediately after the end of the therapies and with follow-up after 1 month.

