### Sample size {14}

The calculation of the sample size considered a difference of 1.5 points between the groups, which would be a clinically relevant value for the outcome of neck pain intensity, as measured using the Numeric Rating Scale (NRS) [64, 66], with an estimated standard deviation of 1.6 points, based on a scientific clinical study [43]. There are a statistical power of 80% and a possible sample loss of 20%, considering individuals who for any reason want to interrupt the intervention. Thus, 84 individuals will be needed in total, 28 in each group (TA, LA, and Sham). The processing of the sample calculation was performed using the Minitab software, v.17, State College, PA.

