## Statistical methods

### Statistical methods for primary and secondary outcomes {20a}

An assessor blinded to the randomization and assessment processes will make the statistical inferences for the primary and secondary outcomes. The intention-to-treat principle will be adopted in the analyses. The normality of the data will be evaluated using the Kolmogorov-Smirnov test. Specific analyses will be used, depending on the distribution (normality and homogeneity) of the data. Parametric and nonparametric analyses will be used for normally and non-normally distributed data, respectively. These analyses will be performed using the SPSS v.17 statistical software (SPSS, Inc., IL, USA), considering a statistical power of 80% for all the tests, with a significance level of *p* < 0.05.

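### The primary outcome is seven NRS scores at two time points in three arms, with p < 0.05 for all tests and none named as decisive, so the primary false-positive rate is well above 5%

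*Protocol article*

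**What the plan says.** The Outcomes section gives the primary outcome in general terms: "The primary outcome will be the pain intensity", measured on the NRS. The primary objective breaks this into pain at rest and in flexion, extension, left and right lateral bending, and left and right rotation. All are to be assessed "immediately after the end of the therapies and with follow-up after 1 month". The Numeric Rating Scale section then states: "All before-after data will be individually recorded and compared for their respective positions". No average, composite, worst score or lead position is mentioned.

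The statistical methods section chooses between parametric and nonparametric analyses by distribution, "considering a statistical power of 80% for all the tests, with a significance level of" p < 0.05.

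All three contrasts between arms are of interest. The abstract's discussion compares laser acupuncture with both needle acupuncture and sham. The Sham section makes sham the control for both active arms. The Implications section asks which active technique works better.

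The sample size section treats pain intensity as one quantity: "The calculation of the sample size considered a difference of 1.5 points between the groups", with an SD of 1.6, 80% power and 20% loss. It concludes that "84 individuals will be needed in total, 28 in each group (TA, LA, and Sham").

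**The concern.** The trial is sized for one score, but its primary objective contains 14 score-by-time results and three possible contrasts for each. Nothing in the document ranks them. Read as written, a significant result at any position and either time could be reported as a positive primary finding, and the 5% error rate would then not apply to the trial's main conclusion.

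Mixed results would also have no agreed reading, for example a difference in left rotation immediately after treatment but none at rest or at 1 month. The definition of the primary outcome belongs in the protocol, and here the protocol does more than stay silent: it sets out several positions, two times, comparison by position and a single threshold.

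**Working it through.** **1. Reproduce the stated sample size.** Inputs from the sample size section: difference 1.5, SD 1.6, power 80%, loss 20%; alpha 0.05 from the statistical methods section.

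- One-way ANOVA, three groups, largest difference 1.5: noncentrality λ = n × 1.5² / (2 × 1.6²) = 0.4395n.
- At n = 23, λ = 10.1 and power is 80.1%, so 23 per arm are needed. 23 × 1.2 = 27.6, rounded up to 28; 28 × 3 = **84**, as stated.
- A two-sample t calculation gives 19 per arm. 19/0.8 = 23.75, rounded up to 24, or 72 in total. The normal approximation gives 18, then 18/0.8 = 22.5, rounded up to 23, or 69.

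The stated figure is therefore what a three-group ANOVA on a single NRS score gives. (Inflating by 23/0.8 would give 29 per arm, or 87. That is a separate minor matter.)

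**2. Count the primary results.** 7 scores × 2 times = 14 score-by-time analyses. 14 × 3 pairs of arms = 42 possible pairwise contrasts.

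**3. Upper figures, if all tests were independent.** 1 − 0.95^14 = 51.2% for 14 omnibus tests. 1 − 0.95^42 = 88.4% for 42 pairwise tests. The scores within a person are correlated and the pairs share arms, so the true figures are lower.

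**4. Allow for correlation.** The document gives no correlations, so these are assumed: 0.5-0.9 between positions and 0.3-0.7 between times. Simulation with no true effect, normal scores, 28 per arm, two-sided tests at 0.05, 20,000 trials per setting. The table shows the chance of at least one p < 0.05:

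| Correlation between positions | Correlation between times | 14 omnibus tests | 42 ungated pairwise tests | One pair of arms, 14 tests |
|---|---|---|---|---|
| 0.5 | 0.3 | 41% | 72% | 40% |
| 0.5 | 0.7 | 37% | 67% | 36% |
| 0.7 | 0.3 | 33% | 61% | 32% |
| 0.7 | 0.7 | 28% | 55% | 28% |
| 0.9 | 0.3 | 22% | 44% | 21% |
| 0.9 | 0.7 | 19% | 39% | 19% |

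With 22 per arm (28 × 0.8 = 22.4) every entry agrees to within about one percentage point.

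**5. Check the remedy.** With one score at one time, three unadjusted pairwise tests give about 12%. An omnibus test at 5% before the pairwise tests gives 5%. The reasoning for three arms is short. If all three arms are equal, the omnibus test limits the error to 5%. If only two are equal, there is just one true pairwise null, and it is tested at 5%.

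The power of the omnibus test for the planned difference is 87.9% with 28 analysed per arm and 78.1% with 22.

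**The case against.** The strongest reply is that the document never writes down 42 tests. It does not say that three pairwise tests follow each score, or that they run without an omnibus test. A threshold of p < 0.05 is also compatible with post hoc p-values that have already been adjusted. The sizing points the same way, since 84 comes from a three-group ANOVA and not from a two-sample calculation. This stands. A reader might infer that 42 tests at 0.05 are planned and that a false-positive primary result is about as likely as not. The documents do not support either statement: the second needs ungated pairwise testing together with a correlation between positions of roughly 0.7-0.9.

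A second reply is that the sentence about comparing positions may only be a matching rule (flexion before with flexion after), and that it speaks of before-after data, not of contrasts between arms or of 1 month. That reading is possible. It does not remove the problem, because the primary objective itself lists all seven scores at both times and no summary of them is given.

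A third reply is that multiplicity adjustment and post hoc procedures are commonly left to an analysis plan that is not shown. That holds for those details, and it also means one cannot say that the decisive result will be picked after the data are seen. It does not hold for the choice of primary endpoint, which the protocol has set as a list.

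**Conclusion.** The concern holds: the primary outcome is set as 14 score-by-time results with one common threshold and no deciding result, while the trial is sized for one. The primary false-positive rate is about 19-41% with an omnibus test for each result, and about 39-72% with ungated pairwise tests. Even within a single pair of arms it is about 19-40%. The lowest of these is more than three times the nominal 5%.

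The size depends on the assumed correlations and on the test procedure, neither of which the document gives, so it should be quoted as a range with those assumptions. The conclusion that the rate is well above 5% does not change anywhere in the range examined.

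**What to change.** Before unblinding, name one primary NRS measure at one time point. Which one is the investigators' choice; rest pain, or the mean of the seven scores, immediately after the session would serve. State that the 1.5-point difference and SD of 1.6 refer to that measure. Make the other positions and the other time point secondary.

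For the primary measure, test the three arms jointly at 5%, then test the three pairs at 5% each only if the joint test is significant. State that only this sequence supports a confirmatory claim.

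The cost is a change of wording in the protocol and analysis plan. The stated 84 is kept, and no extra patients or data are needed. The downside is that the remaining positions and time point lose confirmatory status.

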#### Pressure pain threshold (PPT)

Measurements will be made using a pressure algometer (Somedic®, Hӧrby, Sweden), with the tip of the instrument (1 cm^2^) positioned on cervical zygapophysial joints C5/6 [55], between C7 and the acromion, bilaterally at the midpoint of the upper trapezius muscle [56], and on the middle third of the right tibialis anterior muscle. All these points will be previously marked with a dermatograph pencil. The algometer probe will be positioned perpendicular to the skin, and pressure will be applied at a rate of ~ 40 kPa/s. Three consecutive PPT measurements will be made, with an interval of 30 s between them, and the average value will be recorded. The participants will be instructed to close their eyes and to press the algometer sensor when the pressure sensation becomes painful, with the corresponding value being recorded. A test will be performed to familiarize the individuals with the algometer, explaining the procedure, and a demonstration will be made using the thenar region of the hand. During the actual measurements, the individuals will not be allowed to see the algometer. The intra-examiner reliability of the PPT measurements will be evaluated using measurements at the same points for 10 healthy and asymptomatic individuals, performed by a single examiner at intervals of 48 h. The reliability will then be estimated by calculating intraclass correlation coefficients (ICC) [55–58].

#### Temporal summation of pain (TS)

Measurements will be made using the pressure algometer (Somedic®, Hӧrby, Sweden), applying a total of 10 stimuli, at a rate of 40 kPa/s, using the average value from the previous algometry test performed on the most painful upper trapezius muscle (or the dominant side if there is no evident difference). Each stimulus will be maintained for 1 s, using a timer to ensure the correct intervals (1 s). The individuals will be asked about their pain at the 1st, 5th, and 10th seconds of stimulus, using the NRS. In order to avoid any interference, the test will begin 5 min after the PPT [58, 59].

#### Conditioned pain modulation (CPM)

Cold nociceptive stimulus will be employed. Individuals will receive instructions before the test. Conditioned stimulus will be provided by the hand on the side ipsilateral to the region of the greatest neck pain, which will be immersed for 1 min in a water bath kept at 22 °C, in order to standardize the hand temperature. After that, the same hand will be submerged (up to the wrist) for 1 min in ice water (kept at 4 °C). After 30 s, the individual will be asked to report (using the NRS) the intensity of the pain in the hand, caused by the ice water. After immersion for 1 min, the patient will be asked to remove the hand from the ice water. The PPT will be performed (between C7 and the acromion, at the mid-point of the upper trapezius muscle), using the side contralateral to the immersed hand. The PPT evaluation will be performed before and immediately after the cold stimulus. The mean PPT value before the stimulus will be subtracted from the mean value after the stimulus, with a lower value indicating that the endogenous system is less efficient in inhibiting pain [58, 60, 61].

#### Use of analgesic medicines

It will be important to record the use of analgesic medications, in order to determine whether their use decreased after treatment. The participants will be asked to report all the medications used. This information will be collected and recorded. In tables, the analgesic medications will be converted into opioids, considering the equianalgesic dose of morphine [62] and non-opioids and considering the equianalgesic dose of acetaminophen (paracetamol) [63].

#### Global Perceived Effect Scale (GPE)

The Global Perceived Effect Scale is used to assess the perception of the individual regarding any improvement, comparing the initial symptoms with the current condition. This scale, which has been translated into Portuguese and validated, provides good reliability when applied to musculoskeletal disorders. It uses 11 points, ranging from − 5 (much worse) to 0 (no change) and to 5 (completely recovered). After treatment, the participants will be asked: “Compared to when this problem first started, how would you describe the condition of your neck today?” A higher score indicates an improved condition [64, 65].

### Participant timeline {13}

The participant timeline is presented in Fig. 2.

**Fig. 2 Fig2:**
[figure not shown]
Flow diagram of the randomized clinical trial. NRS, Numeric Rating Scale; PPT, pressure pain threshold; CPM, conditioned pain modulation; GPE, global perceived effect scale

### Sample size {14}

The calculation of the sample size considered a difference of 1.5 points between the groups, which would be a clinically relevant value for the outcome of neck pain intensity, as measured using the Numeric Rating Scale (NRS) [64, 66], with an estimated standard deviation of 1.6 points, based on a scientific clinical study [43]. There are a statistical power of 80% and a possible sample loss of 20%, considering individuals who for any reason want to interrupt the intervention. Thus, 84 individuals will be needed in total, 28 in each group (TA, LA, and Sham). The processing of the sample calculation was performed using the Minitab software, v.17, State College, PA.

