**Methods/design:**

This will be a controlled and randomized clinical trial. Eighty-four individuals will be recruited and distributed equally and randomly into 3 groups: TA (which will receive the acupuncture treatment with needles), LA (which will receive the laser acupuncture treatment), and Sham (who will receive the placebo intervention). The acupuncture points (*Tianzhu*, *Fengchi*, *Jianjing*, and *Jianzhongshu*) will be stimulated bilaterally. The primary outcome will be pain intensity, determined using the Numerical Rating Scale. The secondary outcomes will be pressure pain threshold, temporal summation of pain, conditioned pain modulation, use of analgesic medicines after treatment, and the global perceived effect scale. The assessments will be performed immediately before and after the treatment, which will be a single session, at the follow-up and 1 month after the end of the treatments; evaluation will be made of the pain intensity and the global perceived effect. Statistical analysis of the data obtained will consider a significance level of *p* < 0.05.

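### 80% power is claimed for every test, but only NRS pain intensity was sized; for that outcome 28 per arm appears to be one short after 20% loss

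*Protocol article*

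**What the plan says.** The inputs are in the protocol article under Sample size {14}. "The calculation of the sample size considered a difference of 1.5 points between the groups", for neck pain intensity on the NRS, "with an estimated standard deviation of 1.6 points". The section continues: "There are a statistical power of 80% and a possible sample loss of 20" percent, and concludes "84 individuals will be needed in total, 28 in each group (TA, LA, and Sham"). The software is Minitab v.17. The section names no test, no number of completers and no formula for the loss allowance.

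Under Statistical methods for primary and secondary outcomes {20a}, the analyses are to be run "considering a statistical power of 80% for all the tests", "with a significance level of *p* < 0.05". No correction for multiple comparisons is named.

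Outcomes {12} lists NRS pain intensity as primary. The secondary outcomes are pressure pain threshold (PPT), temporal summation (TS), conditioned pain modulation (CPM), analgesic use and global perceived effect (GPE). The Objectives and Discussion sections put the comparison of traditional acupuncture (TA) with laser acupuncture (LA) at the centre, with sham as control.

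**The concern.** Power belongs to a named test, a stated effect, a variability and a sample size. It is not a setting that can be applied to a whole family of tests at analysis. The article supplies these quantities for one outcome and then claims 80% for all of them. A non-significant result on PPT or CPM could then be read as though the trial had been sized to find an effect there.

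The second question is whether 28 per arm keeps 80% power for NRS itself after the stated 20% loss. It also matters which comparison that power refers to, because an overall three-group test does not say whether TA and LA differ.

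**Working it through.** **Inputs.** Difference 1.5, SD 1.6, power 80%, loss 20%, 28 per arm (Sample size {14}); equal allocation to three arms (Abstract, Methods/design); alpha 0.05 (Statistical methods {20a}). Two-sided testing is my assumption.

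**Outcomes covered by a power calculation.**

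| Outcome | Difference given | SD given |
|---|---|---|
| NRS pain intensity | 1.5 | 1.6 |
| PPT, TS, CPM, analgesic use, GPE | none | none |

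Power for the second row cannot be computed from the article, so 80% for those tests is neither shown nor checkable.

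**Reproducing 28.** For a one-way ANOVA with three groups, extreme means 1.5 apart and the third midway, the noncentrality is λ = n × 1.5² / (2 × 1.6²).

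- n = 22: λ = 9.67, critical F(2, 63) = 3.14, power 78.1%.
- n = 23: λ = 10.11, critical F(2, 66) = 3.14, power 80.1%. So 23 completers per arm are needed.
- 23 × 1.2 = 27.6, rounded up to 28, the printed figure.
- 23 / (1 − 0.20) = 28.75, rounded up to 29 per arm, 87 in total.

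Other routes:

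- A two-group t test at two-sided 0.05 needs 19, and 19 / 0.8 = 23.75, or 24. That is not 28.
- The normal-approximation formula at alpha 0.025 gives 22, and 22 / 0.8 = 27.5, or 28. That alpha appears nowhere in the article. The exact t test at 0.025 has 78.1% power at 22 and needs 23, which again leads to 29.

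**Power for NRS after 20% loss.** 28 × 0.8 = 22.4, so about 22 per arm. For a pairwise contrast the noncentrality at n = 22 is 1.5 / (1.6 × √(2/22)) = 3.11.

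| Test of 1.5 points | 22 per arm | 28 per arm |
|---|---|---|
| Omnibus F, third mean midway | 78.1% (78.9% at 22.4) | 87.9% |
| Pairwise t, unadjusted 0.05 | 85.9% | 93.1% |
| Pairwise, Tukey | 75.9% | 86.6% |
| Pairwise, Bonferroni (0.05/3), pooled error | 74.0% | 85.3% |
| Pairwise, Bonferroni, two-group t | 72.9% | 84.6% |

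**Effect of baseline adjustment.** Take 1.6 as the SD of the post-treatment score, and let r be its correlation with baseline. The residual SD is then 1.6 × √(1 − r²). The article gives no r, so both values here are assumptions. With 22 per arm, Bonferroni and pooled error:

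- r = 0.3: residual SD 1.53, power about 79% (78.5%).
- r = 0.5: residual SD 1.39, power about 87%.

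**The case against.** Five objections deserve an answer.

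- **The route to 28 is inferred.** This is correct. The test, the 23 and the multiplication by 1.2 appear nowhere in the article, and one other route reaches 28. The ANOVA route fits the printed figures at the stated alpha, but it cannot be presented as fact.
- **The shortfall is trivial.** It is one participant per arm, or one to two points of power, set against an SD borrowed from another study. It also uses the least favourable pattern of means: with two arms equal and the third 1.5 away, the F test has 89.1% at 22 per arm. This stands, and it is why the loss allowance is the minor part.
- **All 28 may be analysed.** The sections on exclusion, discontinuation {11b} and retention {18b} say that the most recent data of people who stop will be used under intention to treat. With 28 per arm every row of the table exceeds 80%. That holds only if carried-forward values do not dilute the effect. Even so, it does not rescue the loss allowance, which was added on the premise that data would be lost.
- **The pairwise comparisons are underpowered.** A reader might infer this stronger claim, that 80% is untrue for TA against LA. The article does not support it. At its own 0.05 the pairwise power with 22 per arm is about 86%. It falls below 80% only under a correction that the article does not adopt and that an analysis plan may settle.
- **The 80% phrase is only loose wording.** It may be meant as a conventional target. As written, though, it asserts a property for outcomes that were never sized.

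**Conclusion.** The claim of 80% power across all tests is unsupported. The article sizes NRS pain intensity alone and gives nothing from which power for the five secondary outcomes could be derived. This conclusion rests on the text and needs no assumption.

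The loss allowance is a lesser matter. If the calculation was the three-group ANOVA, 29 per arm (87 in total) was needed rather than 28 (84). With about 22 completers, omnibus power is 78% to 79%, a narrow miss. This assumes two-sided testing, the third mean midway, and analysis of completers only. It is not a finding that the trial is materially underpowered for NRS, nor that the TA against LA comparison lacks 80% power at the stated significance level.

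**What to change.** 1. In Statistical methods {20a}, remove the extension of 80% power to every test and tie the figure to NRS pain intensity. State that the secondary outcomes were not sized.
2. In Sample size {14}, name the test, the completers assumed per arm and the power after 20% loss. If the ANOVA reconstruction is right, the entries are 23 needed, about 22 expected, and about 78% for the F test. Give pairwise power for 1.5 points both ways: about 86% unadjusted, and about 73% to 76% if Bonferroni or Tukey is used.
3. Analyse NRS adjusted for its baseline value, which is already collected. With Bonferroni at 22 per arm this gives about 79% if the correlation is 0.3 and about 87% if it is 0.5, against 74% without adjustment. At the lower correlation it does not quite reach 80% under that correction.

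The cost is a few sentences, a slightly less favourable printed figure, and one covariate in the model. No further patients or measurements are required.
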